
#### 2.5.2. Sham Acupuncture

Needle insertion: In the control acupuncture protocol, needling (single use of needle per session) should be gentle, superficial, and oblique on each shoulder and upper arm at non-acupuncture points. This needling placement does not correspond to any known acupoints; thus, it is unlikely to affect any segment innervation related to ovaries or implicated in PCOS physiology (Table A1 and Figure 1c). Stimulation: No manual stimulation, whether tonify or disperse, will be done during the intervention.

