### 2.5. Intervention

A schedule was established for a total of 12 weeks of intervention, with a frequency of treatment of 1 time per week during the first 6 weeks and 2 times per month in the following 6 weeks. Treatments will take place at a research center/private TCM clinic (Figure 2 and Table 2).

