In short, the combination of Gǔangyúan REN-4 with Tàixī KID-3 and Tàichōng LIV-3, both Earth points, contributes to treat kidney deficiency and tonify liver blood, soothing the liver’s Yang hyperactivity, and rooting the Shen, thus, calming emotions [49]. The sedation of Bàihuì DU-20 may add to the relief of anxiety. On the other hand, Zhōngjí REN-3 and Zhōngwăn REN-12 will also contribute to moving the stagnated Qi associated with phlegm-dampness syndrome. Stimulating points in the lower Triple Burner, namely, Shēnmài BL-62 and Si3 Hòuxī SI-3, we expect an improvement of issues related to food, fluids, blood stasis, accumulated phlegm, and stagnant emotions derived from kidney deficiency associated with phlegm-dampness syndrome. The Qi stagnation observed in these patients usually leads to an imbalance in the transforming function of the Earth element for which Tiānshū ST-25 and Sānyīnjiāo SP-6 may help to restore the Qi and Xue circulation for a general improvement of homeostasis [45]. In women presenting blood stasis, the Conception–Governor vessel circulation is prone to an imbalance that leads to frequent amenorrhea and fertility issues. For that, we suggest regulating the Conception vessel to promote a healthy reproductive cycle by opening Ren Mai and restoring harmony by pairing the Luo points Zhàohăi KID-6 with right Lièquè LU-7 and right Nèiguān P-6 with left Gōngsūn SP-4 to regulate the Conception, Governing, and Penetrating vessels [49]. We would also add Tiānshū ST-25, Guīlái ST-29, and Yīlíngqúan SP-9 to stabilize and harmonize the Earth movement, nourishing blood and eliminate stasis with the spleen’s reinforcement [45]. Based on the characteristics of the referred points, we designed two protocols: Protocol A includes: Zhōngjí REN-3 (dispel), Gǔangyúan REN-4 (tonify), Zhōngwăn REN-12 (dispel), and Tiānshū ST-25 bilaterally (dispel) and Sānyīnjiāo SP-6 bilaterally (tonify). Needles will also be placed in extra segmental acupuncture points: Bàihui DU-20 (sedation), Tàichōng LIV-3 (dispel), Tàixī KID-3 (tonify), Shēnmài BL-62 (dispel), and Hòuxī SI-3 (tonify). In total, 14 needles will be placed (Table A1, and Figure 1a). Protocol B: consists of 16 needles placed in segmental abdominal points; Zhōngjí REN-3 (dispel), Gǔangyúan REN-4 (tonify), Qìhăi REN-6 (tonify), Tiānshū ST-25 (dispel), Guīlái ST-29 (dispel), bilaterally, and extra segmental points: Yīlíngqúan SP-9 bilaterally (tonify), Nèiguān P-6, left Gōngsūn SP-4 (tonify), left Zhàohăi KID-6 (tonify), Tàixī KID-3 (tonify bilaterally), right Lièquè LU-7 (tonify), and Bàihuì DU-20 (sedate) (Table A1 and Figure 1b). Needles and insertion: disposable 25 **×** 25 needle will be used. Insertion depth will be 15–35 mm into skeletal muscle or fibrous tissue. The depth of needle insertion could vary according to the location depth of the acupoint between patients depending on body mass index (BMI), as depth should be enough to reach muscle/fibrous tissue. Stimulation: When needles are inserted, they will be stimulated by manual rotation circa 180 degrees back and forth to evoke tingling sensation—so called de Qi—reflecting activation of sensory afferents. As soon as Qi sensation is reached, the needle should not hurt or cause any pain or discomfort. After 10 min, needles will be stimulated manually. This should be repeated after 20 min and again after 30 min. Two sets of acupuncture points will be used according to the symptoms of each study group.

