## 3. Results

The target of this study focuses on four types of parameters divided into primary, secondary, and exploratory outcomes. Primary outcomes refer to hormonal parameters, and secondary to anthropometric and metabolic parameters. Exploratory outcomes are related to quality-of-life analysis and will be performed using the Medical Outcomes Study 36-Item Short Form Health Survey [50], the Zung Self-Rating Anxiety Scale [51], and the Zung Self-Rating Depression Scale [52] (Table 3). All the questionnaires used are validated for Portuguese language. Outcome measures will be collected at baseline, 6 weeks, 12 weeks, and 6 months after the last acupuncture treatment (Table 2).

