### 3.1. Blinded

A random code and blind code will be conducted by a “third party” independent of the study using opaque envelopes. The envelopes will be sealed and shuffled, and the assignment records will not be disclosed until the end of the study. Trial participants, formal physicians, therapists, outcome assessors, and data analysts will be blinded to the treatment allocation to minimize potential sources of bias. Only acupuncturists will not be blinded to the treatment allocation. Licensed acupuncturist profile with at least five years of experience will be recruited and will be trained to administer acupuncture. The techniques for the entire treatment procedure will be standardized between practitioners. Results will be kept sealed until the end of the intervention phase. Data analysis will be conducted independently by an experienced statistician, independent of the research team.

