**Figure 2 healthcare-10-01999-f002:**
[figure not shown]
Flowchart of the study period.

**Table 1 healthcare-10-01999-t001:** Rotterdam phenotypes for PCOS women with correspondent TCM phenotype.

Phenotype	Description
Rotterdam Phenotype A (classical PCOS) [46]	Hyperandrogenism + polycystic ovary morphology + ovulatory dysfunction—28.7%
TCM phenotype [47]	Spleen deficiency and phlegm stasis SP’s—32.27%
Rotterdam Phenotype B [46]	Hyperandrogenism + Ovulatory disfunction—19.0%
TCM phenotype [47]	Phlegm stasis and blood stasis—16.55%
Rotterdam Phenotype C [46]	Ovulatory disfunction + polycystic ovary morphology—37.3%
TCM phenotype [47]	Kidney deficiency and liver stasis—40.29%
Rotterdam Phenotype D [46]	Hyperandrogenism + polycystic ovary morphology—15.0%
TCM phenotype [47]	Kidney deficiency and blood stasis—10.89%

**Table 2 healthcare-10-01999-t002:** SPIRIT schedule of enrolment, interventions, and assessments.

	STUDY PERIOD														
	Enrolment	Allocation	Post-Allocation												Close-Out
TIMEPOINT	*−1 month*	0	* _W1_ *	* _W2_ *	* _W3_ *	* _W4_ *	* _W5_ *	* _W6_ *	* _W7_ *	* _W8_ *	* _W9_ *	* _W10_ *	* _W11_ *	* _W12_ *	*After 6 months*
ENROLMENT:															
Eligibility screen	X														
Informed consent	X														
Baseline assessments	X														
Allocation		X													
INTERVENTIONS:															
Active acupuncture															
		X	X	X	X		X		X		X		X	
Sham acupuncture															
		X	X	X	X		X		X		X		X	
ASSESSMENTS:															
*Diagnostic examination*	X														
*Primary and secondary outcomes*		X						X						X	X
*Life quality related questionnaires*	X	X						X						X	X

**Table 3 healthcare-10-01999-t003:** Primary, secondary, and exploratory outcomes that will be used in the study.

Primary	Secondary	Exploratory
**Hormonal Parameters**: Modified Ferriman-Gallwey score Ludwig visual score LH, mean (SD), mIU/mL FSH, mean (SD), mIU/mL LH/FSH Total free testosterone Androstenedione Progesterone, median (IQR), ng/mL Estradiol, median (IQR), pg/mL Sex hormone–binding globulin (SHBG), mean (SD), μg/mL Ovulation rate (%)	**Anthropometric parameters** Age (years) Height (cm) Weight (Kg) BMI (kg/m^2^) Waist circumference (cm) Waist Hip Ratio	**Quality-of-life scores**: Medical Outcomes Study 36-Item Short Form Health Survey Zung Self-Rating Anxiety Scale Zung Self-Rating Depression

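### Active sessions carry three timed hands-on rounds that have no counterpart in sham, so practitioner contact may contribute to differences on the exploratory SF-36 and Zung scales (minor)

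*Protocol article*

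**What the plan says.** **Active arm (section 2.5.1).** Needles are rotated at insertion until de Qi is felt. A timed sequence follows: "After 10 min, needles will be stimulated manually", and then "This should be repeated after 20 min and again after 30 min". Protocol A uses 14 needles and Protocol B uses 16.

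**Sham arm (section 2.5.2).** Needling is superficial, at non-acupuncture sites on the shoulders and upper arms. On stimulation the section says only: "No manual stimulation, whether tonify or disperse, will be done during the intervention". It gives no retention time and no timed check. The sham rows of Table A1 add site, innervation and action, but nothing on timing.

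**Schedule (section 2.5 and Table 2).** Treatment is "1 time per week during the first 6 weeks and 2 times per month in the following 6 weeks", without distinction by arm. Table 2 ("SPIRIT schedule of enrolment, interventions, and assessments") marks the same number of sessions for active and sham.

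**Blinding (section 3.1).** "Only acupuncturists will not be blinded to the treatment allocation". Participants and outcome assessors are stated to be blinded. On uniformity of treatment: "The techniques for the entire treatment procedure will be standardized between practitioners".

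**Outcomes (section 3).** "Exploratory outcomes are related to quality-of-life analysis"; these are the SF-36 and the two Zung scales. Section 4.3 anticipates better scores on them following active treatment, and section 5 lists emotional symptoms among what the trial is to evaluate.

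**The concern.** A sham control should leave the needling under test as the difference between arms. Here a second difference comes with it. The practitioner handles the needles at three set times in every active session, and the sham description removes the reason for doing so without putting a neutral contact in its place.

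Anxiety, depression and quality of life are reported by the woman herself, and practitioner attention is a plausible influence on all three. Blinding does not remove this: a woman who does not know her arm still receives more or less contact. No later analysis can separate the two either, because if contact differs it differs completely by arm.

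At stake is how a favourable SF-36 or Zung result would be read. It could be credited to the acupuncture protocol when part of it came from contact.

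**Working it through.** The article gives no figure to reproduce here. The check is a comparison of the two procedures and a count.

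**Side by side, within a session**

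| Element | Active (2.5.1) | Sham (2.5.2, Table A1) |
|---|---|---|
| At insertion | Rotation to de Qi | Superficial needling, no stimulation |
| 10 min | Manual stimulation | None; no other contact described |
| 20 min | Manual stimulation | None; no other contact described |
| 30 min | Manual stimulation | None; no other contact described |
| Retention time | Not stated; at least 30 min is implied by the last round | Not stated |

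The insertion step is left out of the count, because sham women are also being needled at that moment.

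**Between sessions.** Table 2 gives both arms the same number of sessions, so any imbalance in contact arises within sessions and not from the number of visits.

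**Does another sentence close the gap?** The standardization sentence in section 3.1 concerns uniformity among practitioners. It does not say that time or contact is the same in the two arms.

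**Count of rounds per active woman**

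- Rounds per session: 10, 20 and 30 min = 3.
- Sessions from section 2.5: 6 weekly, plus 2 per month over 6 weeks (about 1.5 months): 6 + 2 × 1.5 = 9.
- Sessions from the marks in Table 2 as extracted: 8 per arm.
- Rounds over the course: 3 × 9 = 27, or 3 × 8 = 24.
- Equivalent timed contacts described for sham: 0.

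**Outcomes exposed.** The SF-36 and both Zung scales are self-reported and so are open to an effect of contact. Hormone and metabolic values come from the laboratory. The modified Ferriman-Gallwey and Ludwig scores would come from assessors stated to be blinded. These two kinds of outcome are little exposed.

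**Effect size.** The documents give nothing from which a contact effect on these scales could be sized, so no bias or error rate is calculated.

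**The case against.** The strongest reply is that this is silence in a condensed article. Sham retention time and conduct during the session are details that a full protocol or treatment manual often holds. Section 3.1 says that acupuncturists will be trained, so further instructions may well exist. The active section gives no total session length either. Taken alone, the missing sham duration is weak evidence, and that part of the reply stands.

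The reply does not dispose of the stated contrast. The article times the active procedure to the minute and then says, for sham, that the activity filling those times will not take place. That is a described difference between arms and not only a missing detail.

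A reader might go further and infer that sham women are left alone, that their sessions are shorter, or that active women receive three extra visits from a practitioner who has left the room. The documents support none of these. They show three manual stimulations against none. They do not say that the acupuncturist leaves and returns, and section 2.5.2 does not address presence or duration. If the acupuncturist attends both arms alike, only the needle handling differs.

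Nor is withholding stimulation a fault. It is a deliberate part of the sham and should stay.

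It is also fair to say that little hangs on the point. The scales are exploratory, each woman sees only one procedure and may stay unaware of her arm, and larger differences between arms (site, depth, number of needles, de Qi) would remain after any matching of contact.

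**Conclusion.** The point holds as a minor design weakness with a cheap improvement. Carried out as described, the unblinded acupuncturist has three hands-on contacts per active session, 24 to 27 per woman over the course, with no counterpart in sham. Part of any SF-36 or Zung difference could therefore reflect practitioner contact rather than needling.

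This rests on two assumptions: that no fuller document already prescribes matched contact for sham, and that contact of this kind can move self-reported scores. How far it would move them is unknown and may be nothing. The main hormonal and metabolic conclusions are not called into question. Confidence is medium, mainly because the article may condense a fuller text.

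**What to change.** Add one sentence to section 2.5.2: *Sham needles are retained as long as active needles, and the acupuncturist checks them at 10, 20 and 30 min without manipulating them.* The no-stimulation sentence stays, and so does the contrast under test. If a fuller protocol already says this, copying the sentence into the article is enough. The change has to be in place before treatment starts.

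**Cost**

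- Sham women: 30 in each of the two TCM groups, 60 in all (section 2.2).
- Checks: 60 × 8 × 3 = 1440, or 60 × 9 × 3 = 1620.
- Time at an assumed 1 to 2 min per check: from 1440 × 1 / 60 = 24 hours to 1620 × 2 / 60 = 54 hours over the whole trial.

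No added visit, staff member or procedure is needed. With the sentence in place, the described imbalance in timed contact falls from 3 per session to 0. It evens out contact only. Expectation arising from needle site, depth, number and de Qi is not removed.

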## 3. Results

The target of this study focuses on four types of parameters divided into primary, secondary, and exploratory outcomes. Primary outcomes refer to hormonal parameters, and secondary to anthropometric and metabolic parameters. Exploratory outcomes are related to quality-of-life analysis and will be performed using the Medical Outcomes Study 36-Item Short Form Health Survey [50], the Zung Self-Rating Anxiety Scale [51], and the Zung Self-Rating Depression Scale [52] (Table 3). All the questionnaires used are validated for Portuguese language. Outcome measures will be collected at baseline, 6 weeks, 12 weeks, and 6 months after the last acupuncture treatment (Table 2).

### 3.1. Blinded

A random code and blind code will be conducted by a “third party” independent of the study using opaque envelopes. The envelopes will be sealed and shuffled, and the assignment records will not be disclosed until the end of the study. Trial participants, formal physicians, therapists, outcome assessors, and data analysts will be blinded to the treatment allocation to minimize potential sources of bias. Only acupuncturists will not be blinded to the treatment allocation. Licensed acupuncturist profile with at least five years of experience will be recruited and will be trained to administer acupuncture. The techniques for the entire treatment procedure will be standardized between practitioners. Results will be kept sealed until the end of the intervention phase. Data analysis will be conducted independently by an experienced statistician, independent of the research team.

### 3.2. Adverse Events/Serious Reactions

Adverse events will be monitored for each treatment during the trial. Any adverse events or reactions that are thought to be causally associated with the intervention will be recorded, managed, and reported to the study coordinators. Serious adverse events or severe adverse reactions will be defined according to the International Harmonization Harmonized Tripartite Guideline and reported to the ethical committee.

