## Abstract

(1) Background: Human polycystic ovary/ovarian syndrome (PCOS) is linked to endocrine, metabolic, and psychological complications. We propose a randomized controlled pilot study for an acupuncture protocol regarding the management of PCOS symptoms based on TCM diagnosis; (2) Methods: We will randomly allocate 120 women diagnosed with PCOS into two groups. The study group will be treated with acupuncture for points known to act upon the autonomous regulation of the hormonal, metabolic and emotional components. (3) Results and Conclusions: We expect to provide evidence of high methodological quality related to the effects and safety of an acupuncture protocol based on the perspective of a TCM diagnostic.

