### 4.3. What We Expect with the Trial

With the proposed trial, we expect to validate an acupuncture protocol in terms of efficacy and safety that can be a useful tool in the management of symptoms associated with PCOS. With this study design, we expect to find evidence that active acupuncture can be more helpful for promoting follicular development, adjusting the menstrual cycle, and increasing ovulation rate in women with PCOS than sham acupuncture and the long-term effect of the treatment. After active acupuncture treatment, it is expected to find a relative reduction of the biomarkers when comparing to baseline values regarding LH, LH/FSH, total free testosterone, androstenedione, estradiol, BMI, waist circumference, WRH, modified Ferriman–Gallwey score, and Ludwig visual score. We expect an improvement of biochemical hyperandrogenism and HPG axis imbalance, a decrease of androstenedione and sex-hormone-binding globulin, besides the expected decrease in the levels of LH, LH/FSH ratio, total testosterone, estradiol, and on the scoring of the modified Ferriman–Gallwey and Ludwig scales. We expect a possible increase in FSH, progesterone, and the ovulation rate after active acupuncture. With respect to secondary outcomes, we will explore the effect of the acupuncture treatment on metabolic symptoms and expect to describe the metabolic profile of each phenotype before and after the respective treatment. We will adopt international measures as a gold standard for assessing the metabolic status criteria. Besides HOMA-IR improvement, we expect to find a positive correlation between active acupuncture and reduction of the levels of triglycerides, total cholesterol, LDL-C, LDL/HDL, fasting glucose, fasting insulin, and serum insulin and an overview improvement of the metabolic syndrome development. In addition to that, we will try to understand the efficacy of the treatment on exploratory parameters related to the quality of life of the patient, many times disregarded in this type of treatment, especially in anxiety and depression scoring. In this regard, we expect to find a better scoring in the respective questionnaires (reduction in the scoring points of Zung Depression and Anxiety scales and a gain of points in the SF-36 questionnaire) after active acupuncture intervention, particularly in phenotypes where liver fire associated with kidney deficiency originates a lack of mental presence or easy loss of temper. With the results of the study, we also expect to obtain evidence on the possible correlation of phenotypes based on the Rotterdam criteria and those based on the TCM diagnosis proposed by Wang et al., 2017.

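### The stated recording rule keeps only those non-serious adverse events judged to be caused by the intervention, so any active-versus-sham comparison of them is open to attribution bias

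*Protocol article*

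**What the plan says.** Section 3.2 of the protocol article has three sentences.

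- Monitoring carries no causality condition: "Adverse events will be monitored for each treatment during the trial".
- Recording does: "Any adverse events or reactions that are thought to be causally associated with the intervention will be recorded".
- Serious events have their own route, again without a causality condition on serious adverse events: "Serious adverse events or severe adverse reactions will be defined according to the International Harmonization Harmonized Tripartite Guideline and reported to the ethical committee".

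On blinding, section 3.1 says "Trial participants, formal physicians, therapists, outcome assessors, and data analysts will be blinded to the treatment allocation", and then "Only acupuncturists will not be blinded to the treatment allocation". Neither section says who judges whether an event was caused by the intervention, or who writes it down.

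Safety is a stated aim. The abstract says "We expect to provide evidence of high methodological quality related to the effects and safety of an acupuncture protocol", section 4.3 says "we expect to validate an acupuncture protocol in terms of efficacy and safety", and section 5 repeats the promise. Table 3 lists no safety outcome, and section 3.3 names no adverse-event analysis.

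**The concern.** The recording rule selects events on a judgement of cause before they enter the database. That has two consequences.

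First, a non-serious event that nobody connects with needling is lost under the rule as written. This matters most for unexpected harms, and for events between sessions or during the 6-month follow-up, when monitoring tied to each treatment does not obviously reach the participant.

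Second, the judgement can differ by arm. Active treatment is 14 or 16 needles in trunk, limbs and head, inserted 15–35 mm and manipulated several times (section 2.5.1). Sham is superficial needling of shoulder and upper arm without stimulation (section 2.5.2). The same abdominal complaint is easier to blame on abdominal needles than on a shoulder needle. The one role that must be present at every treatment, the acupuncturist, is also the one unblinded role. If that person influences which events count as related, the arm difference in recorded events mixes harm with attribution.

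A later analysis plan cannot repair this, because events that were never recorded cannot be analysed.

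**Working it through.** The protocol gives no adverse-event rate and no safety calculation, so there is no figure to reproduce. The check has two parts.

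**1. Routes into the data under section 3.2**

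| Type of event | Condition for recording or reporting | Lost if nobody suspects needling? |
|---|---|---|
| Serious adverse event | Reported to the ethics committee, no causality condition | No |
| Non-serious, thought causally related | Recorded and reported to the coordinators | No |
| Non-serious, not thought related | Monitored, but no recording provision | Yes |

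The gap is the third row.

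**2. How far attribution could move the comparison (illustration)**

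Inputs from the documents: 30 active and 30 sham in each of two diagnostic groups (section 2.2), hence 30 + 30 = 60 per arm; 20% withdrawal (section 2.2), hence 60 × 0.8 = 48 per arm; significance at 0.05 (section 3.3). I take the test as two-sided, which the article does not state.

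Assumed inputs: a true event rate of 20% in both arms, and the share of events judged related in each arm. The documents give neither.

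Recorded rate = true rate × share judged related. With equal true rates, the recorded risk ratio is simply the ratio of the two shares.

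Chance of a significant result ≈ Φ[(d − 1.96 × se0) / se1], where d is the difference in recorded rates, p̄ their mean, se0 = √(2p̄(1 − p̄)/n) and se1 = √((p1(1 − p1) + p2(1 − p2))/n).

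Worked case, 80% versus 20% attributed, n = 60:
- Recorded rates are 0.20 × 0.80 = 0.16 and 0.20 × 0.20 = 0.04, so d = 0.12 and p̄ = 0.10.
- se0 = √(2 × 0.10 × 0.90/60) = 0.0548.
- se1 = √((0.16 × 0.84 + 0.04 × 0.96)/60) = 0.0537.
- Φ[(0.12 − 0.107)/0.0537] = Φ(0.24) = 0.59.

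| Share judged related, active vs sham | Recorded rates | Risk ratio | Chance of p < 0.05, 60 per arm | 48 per arm |
|---|---|---|---|---|
| 80% vs 80% | 16% vs 16% | 1.0 | 5% (nominal) | 5% (nominal) |
| 80% vs 50% | 16% vs 10% | 1.6 | 16% | 14% |
| 80% vs 30% | 16% vs 6% | 2.67 | 42% | 34% |
| 80% vs 20% | 16% vs 4% | 4.0 | 59% | 50% |

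The choice of test matters too. For the last row at 60 per arm, exact enumeration gives 62% with an uncorrected chi-square test and 48% with Fisher's exact test; at 48 per arm Fisher's test gives 35%.

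The filter can also hide a real difference. With true rates of 30% versus 15% and shares judged related of 40% versus 80%, the recorded rates are 0.30 × 0.40 = 12% and 0.15 × 0.80 = 12%.

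If all events are recorded, the shares drop out: equal true rates then give an expected difference of zero and the nominal 5% error.

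**The case against.** The strongest reply has four parts.

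- *Serious harms are covered.* This stands. A reader might infer from the recording sentence that unsuspected events of every kind vanish. The third sentence of section 3.2 does not support that for serious events, and the first sentence says that adverse events in general are monitored. The point is confined to non-serious events.
- *Nobody says the acupuncturist rates causality.* This also stands. It is tempting to read the plan as having an unblinded person decide causality, but no sentence says so. The assessor could be one of the blinded physicians, and naming that person is detail that a condensed article may leave to a fuller protocol. What can be criticised is the stated filter, with nothing in the text that protects it from knowledge of allocation.
- *No between-arm safety analysis is claimed.* Correct. One might infer that the trial cannot compare safety as it claims. The article promises evidence on safety and validation of the protocol, not an explicit safety comparison, and related events could still be compared with a risk of bias. But with a sham arm, that comparison is the one readers will make.
- *The illustration depends on its assumptions.* Agreed. At 70% versus 60% attributed (14% versus 12% recorded), the exact chi-square chance at 60 per arm is 6%, near nominal.

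None of this removes the restriction itself, which is stated text and not an omission.

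**Conclusion.** The concern holds for non-serious adverse events. As written, section 3.2 records them only when someone thinks the intervention caused them, so unsuspected events have no stated route into the data and any active-versus-sham comparison is open to differential attribution. That weakens, but does not abolish, the safety evidence that the article promises.

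The size of the bias in this trial cannot be known from the document. With an assumed true rate of 20% in both arms and 60 per arm, the chance of a spurious significant difference ranges from about 5% to about 60% as attribution goes from equal to 80% versus 20%. The upper figure rests on one extreme pair of assumed shares and shows what is possible, not what is likely.

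The hormonal primary outcomes are unaffected, the study is called a pilot, and serious events are reported regardless of cause. I rate this as should-fix.

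**What to change.** Amend section 3.2 before the first participant is enrolled:

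1. Record all adverse events in both arms, whatever the suspected cause, from allocation to the 6-month visit.
2. Elicit them with the same open question at every treatment session and every assessment visit.
3. Have causality rated afterwards, as a separate step, by a physician or outcome assessor already blinded under section 3.1, from a description that does not reveal needle sites.
4. Report all-cause event rates by arm with 95% confidence intervals for the difference, and events judged related as a subset.

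The visits and the blinded roles already exist. The cost is a reworded paragraph, one form, one standard question and a little more recording.
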